### Study design

3.2

Trial duration will be approximately 26 months for each patient, however, the actual treatment phase will cover only 1.5 months (**Figure 3**). During that time, patients will receive two vaccine doses of AML-VAC-15, six weeks apart, administered subcutaneously into the skin of the lower abdomen. If an insufficient T cell response is measured four weeks after the second vaccination, a booster vaccination may be applied four months after the second vaccination, which will then be followed up with an extra safety visit four weeks later. This particular dosing scheme is based on results of our previous vaccination trials in healthy adults (P-pVAC-SARS-CoV-2, NCT04546841) (25), cancer patients with B cell/antibody deficiency (B-pVAC-SARS-CoV-2, NCT04954469) (26), glioblastoma patients (GLIO-XS15, NCT04842513) and patients with chronic lymphocytic leukemia (CLL) (XS15-iVAC-CLL01, NCT02802943). Data available from those studies so far shows that the dose of 300 µg per peptide adjuvanted with the TLR1/2 ligand XS15 (50 µg) emulsified 1:1 in Montanide ISA 51 VG is safe and effective to induce profound and long lasting CD4^+^ and CD8^+^ T cell responses that by far exceed those induced by previous peptide vaccines as well as by mRNA-based vaccines (25, 26). Therefore, to balance minimal side effects with maximum immune response induction, two vaccinations spaced six weeks apart are applied within the trial, with the option of a booster for those patients whose T cell responses are still insufficient after two vaccinations.

**Figure 3 f3:**
[figure not shown]
Study schedule. AML patients receive two vaccine doses (V1 and V2), six weeks apart. After one month, an end-of-treatment (EOT) visit is scheduled, followed by two follow-up visits (FU1 and FU2), three months apart. Evaluation of immune response by IFN-γ ELISpot assay is done at every visit except screening. If immune response at EOT is insufficient, a booster vaccination (B) can be applied at FU1, which will then be followed by an additional follow-up visit (FU-B) after one month. After FU2, two more follow-up visits (FU3 and FU4) and an end of study (EOS) visit are performed, spaced six months apart. Throughout the study, any ongoing therapy and its monitoring are conducted by the primary responsible hematologist/oncologist. CR, complete remission; CRi, complete remission with incomplete blood count recovery; n, number.

During the follow-up period, patient care will be supervised by the primary responsible hemato-oncologist center, but patients will report every six months for evaluation of safety, toxicity and primary efficacy, defined as the immunogenicity of the vaccine. Same as during treatment phase, at each scheduled visit the number of AEs according to CTCAE V 5.0 will be recorded and the induction of a T cell response will be determined by IFNγ ELISpot.

### Safety and toxicity

3.3

Results of repeated safety assessments performed from screening through EOS at scheduled intervals throughout the trial, recruitment rates and trial status will be presented to an independent data and safety monitoring board (DSMB), comprising independent experts in the field of hematology, oncology and immunology. They will evaluate progress, safety data and critical efficacy endpoints in meetings taking place once a year. An extraordinary meeting may be arranged at any time if patient safety appears to be jeopardized (for example, in case a vaccine-related SAE occurs). Thus, the DSMB will regularly assess whether any stopping rules defined in the protocol have been reached and will formulate recommendations for the sponsor on whether to modify, continue or terminate the trial. General stopping rules in this case are an unacceptable profile or incidence rate of adverse events revealed in this or any other study in which at least one of the investigational products of this trial is administered (predefined as the occurrence of more than three vaccine-related SAEs), a demonstration that the study treatment is ineffective or insufficiently active, a significant number of deaths associated with the study treatment and any other factor that in the view of the sponsor constitutes an adequate reason for terminating the study as a whole.

### Statistical considerations

3.4

According to usual practice in early phase I studies, statistical planning is designed so that a statistically reasoned decision regarding a subsequent phase II study (for or against) can be made. The trial’s sample size was chosen based on the assumption that, in case of the induction of a peptide-specific immune response in ≤ 30% of patients the therapeutic concept will be extended with a probability of at most 5% (type one error, one-sided). Contrastingly, in case of the induction of a peptide-specific immune response in ≥ 60% of patients, the therapeutic concept should be followed with a probability of at least 80% (power). Given a sample size of n = 20 patients, this entails that at least 10 patients must show an immune response for the therapeutic concept to be evaluated in a phase II study. The exact power is 87%, the exact type 1 error is 4.8% (with calculations based on the binomial distribution with n = 20, p = 0.3 or p = 0.6, k < 10 or k ≥ 10).

## Objectives and endpoints of the study

4

One primary objective of the trial is to evaluate the safety and tolerability of the multi-peptide vaccine AML-VAC-XS15, as determined by the number of adverse events (AEs) according to the common terminology criteria for adverse events (CTCAE) V 5.0. The second primary objective of the trial is to evaluate the efficacy, defined as the immunogenicity, of AML-VAC-XS15 as determined by induction of T cell immunity. This will be evaluated by the percentage of patients with induction of a peptide specific T cell response until 28 days after last vaccination compared to baseline before first vaccination by interferon (IFN) γ enzyme-linked immunosorbent spot (ELISPot), using T cells from peripheral blood.

Secondary objectives of this trial include the induction of peptide specific T cell responses until end of study (EOS), as well as safety and toxicity of the peptide vaccine until EOS. For this purpose, the percentage of patients with induction of a peptide specific T cell response at all scheduled visits after vaccination will be calculated, using T cells from peripheral blood, and the number of patients receiving a booster vaccination will also be documented. Incidence and severity of AEs, serious AEs (SAEs) and suspected unexpected severe adverse reactions (SUSARs) will be documented from first vaccination until EOS. Additional secondary objectives include evaluation of first signs of clinical efficacy, determined by progression-free (PFS) and overall survival (OS) defined as the time from baseline (prior to first vaccination) to the first objective leukemia progression, allogeneic stem cell transplantation or death from any cause until EOS. Finally, secondary objectives include quality of life, analyzed by overall Quality of life scores (EORTC QLC C-30) at all visits during and after vaccination.

Exploratory objectives of the trial are to correlate the inducibility of AML-VAC-XS15 immune responses with clinical, biological, and immunopeptidome-based patient characteristics, as well as a further characterization of the phenotype and functionality of vaccine-induced T cells, which should also enable detection of possible T cell exhaustion. Induction of T cell responses will be determined by IFN-γ ELISpot assays at regular timepoints throughout the trial, compared to baseline and correlated with patient characteristics, as assessed at baseline through to the EOS visit. The vaccine-induced T cell response will be characterized by phenotype and functionality analysis of peptide-specific T cells using flow cytometry and single cell sequencing. These analyses will be correlated to alterations in the number and percentage of lymphocyte subset counts from baseline through EOS. Specific analyses of bone marrow-derived T cells will be conducted as well within expanded exploratory endpoints.

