## Introduction

1

Acute myeloid leukemia (AML), a malignant disorder of the bone marrow characterized by the clonal expansion and differentiation arrest of myeloid progenitor cells (1), is the most common form of acute leukemia in adults, yet shows the worst outcome of all leukemias with a 5-year survival rate of only 30% (2). Despite numerous treatment advances in recent years and high initial remission rates, disease relapse occurs in a large proportion of patients, resulting in the still very high mortality rate of AML (3). Most treatment advances that were achieved over the last decades have mainly led to a benefit for younger patients, as they tend to be based on intensive chemotherapy and the increased use of allogeneic stem cell transplantation. Moreover, attempts to find treatment strategies based on the increasing knowledge on the molecular subgroups of AML have led to the approval of a number of new substances like enasidenib, ivosidenib or gilteritinib. However, none of them have so far shown a significant impact on overall survival (4). The prognosis for medically unfit patients and patients above the age of seventy remains dismal due to their ineligibility for intensive treatment and the resulting high relapse rates (5, 6). The main reason for disease relapse is the presence of minimal residual disease (MRD), which is characterized by the persistence of therapy-resistant leukemia stem and progenitor cells (LPCs) in the patients’ bone marrow (7). To eliminate these cells and achieve long-lasting remissions and potential cure, the development of novel therapeutic approaches that specifically target these residual cells is urgently needed.

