Ability to understand and willingness to sign a written informed consent document.Males or females aged ≥ 18 years of age.Documented diagnosis of AML according to WHO guidelines.o Morphological CR or CRi, positive MRD is permitted.o Completion of previous intensive therapy (first vaccination 4-28 weeks after last application of intensive chemotherapy).o Ongoing low intensity treatment, e.g. with hypomethylating agents (HMA) and venetoclax, is permitted.o Ongoing maintenance treatment, e.g. with oral azacytidine or midostaurin, is permitted.o Not eligible for allogeneic stem cell transplantation.Eastern Cooperative Oncology Group (ECOG) performance status score of ≤ 2.Adequate organ function laboratory values.o Bilirubin ≤ 3 times upper limit range [exception isolated indirect hyperbilirubinemia (Morbus Gilbert-Meulengracht)].o Alanine aminotransferase and aminotransferase, ≤ 5 times upper limit range.o Creatinine clearance > 30 ml/min (according to Chronic Kidney Disease Epidemiology Collaboration formula).o Platelets > 50.000/μl.o Absolute CD3^+^ T cell count ≥ 200/μl.Negative serological Hepatitis B test or negative PCR in case of positive serological test without evidence of an active infection, negative testing of Hepatitis C RNA, negative HIV test within 6 weeks prior to study inclusion.Female patients of childbearing potential and male patients with partners of childbearing potential, who are sexually active, must agree to the use of two effective forms (at least one highly effective method) of contraception. This should be started from the signing of the informed consent and be continued until 3 months (both female and male patients) after last vaccination).For female patients of childbearing potential two negative pregnancy tests (sensitivity of at least 25 U/mL) prior to first vaccination, one at screening and the other prior (< 24 h) to first vaccination.Postmenopausal or evidence of non-child-bearing status.

Exclusion criteria

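### Overall survival shares one definition with PFS (first of progression, allograft or death), so OS as written is not time to death and can only be understated

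*Protocol article*

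**What the plan says.** The definition is in the protocol article, section 4 (Objectives and endpoints of the study), among the secondary objectives. The aim is introduced as "Additional secondary objectives include evaluation of first signs of clinical efficacy". The measures and their definition follow in the same sentence: "progression-free (PFS) and overall survival (OS) defined as the time from baseline (prior to first vaccination) to the first objective leukemia progression", and the event list then ends with "allogeneic stem cell transplantation or death from any cause until EOS".

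Three other places bear on how the definition would work:

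- Section 3.2 (Study design) sets the observation window: "Trial duration will be approximately 26 months for each patient".
- The inclusion criteria in section 3.1 (Participants) require patients to be "Not eligible for allogeneic stem cell transplantation".
- The Introduction says of AML in general that "disease relapse occurs in a large proportion of patients".

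No other section defines OS. The Introduction mentions overall survival only as background on other drugs.

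**The concern.** An endpoint that stops at the first of progression, transplantation or death is a PFS-type composite. OS normally has one event, death. When both labels carry the composite, three things follow if the text is applied as written:

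- PFS and OS coincide for every patient, so the second endpoint adds no information.
- A patient alive after relapse becomes an OS event on the relapse date, and the survival time after relapse drops out of the endpoint.
- The resulting figure is labelled OS but cannot be set beside OS from any other source. In a single-arm trial, an outside comparison is the only way to give a survival figure context.

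**Working it through.** **Step 1. Can the sentence be read as two definitions?** Three features of the text speak against it.

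- One defining clause follows both endpoint names, and nothing such as 'respectively' assigns events to endpoints.
- Three events are listed for two endpoints, so the list does not divide into one event set each.
- The clause refers to the first event, which is the language of a composite.

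No separate OS definition appears elsewhere in the article.

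**Step 2. Direction of the error.** Let T_C be the time to the first of progression, transplantation or death, and T_D the time to death. Death is one of the three events, so T_C ≤ T_D for every patient. The composite curve therefore lies on or below the true OS curve at every time point. The two are equal only if nobody is alive after a progression or transplantation.

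**Step 3. Which event matters.** Enrolled patients are not transplant candidates, so transplant events should be few. Progression is the event that would separate the two curves.

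**Step 4. The plan's own figures.** The only sizing figures in the article are in section 3.4 and concern immune response: n = 20, at least 10 responders, response rates 0.30 and 0.60. Exact binomial tails reproduce them:

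- P(X ≥ 10 | 20, 0.30) = 0.0480 (stated 4.8%)
- P(X ≥ 10 | 20, 0.60) = 0.872 (stated 87%)

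Neither depends on PFS or OS, so correcting the OS definition leaves them unchanged.

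**Step 5. Illustrative size.** The article gives no relapse or survival rate. All inputs here are assumptions:

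- median time to relapse m = 12, 18 or 24 months, hazard λ = ln 2 / m
- death without relapse at hazard μ = 0.005 per month (0.5%)
- median survival after relapse r = 3, 6 or 12 months, hazard ν = ln 2 / r
- exponential times, no transplants, t = 24 months

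Formulas:

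- Composite: S_C(t) = exp(−(λ + μ)t)
- Alive after relapse: G(t) = λ [exp(−νt) − exp(−(λ + μ)t)] / (λ + μ − ν)
- True OS: S_D(t) = S_C(t) + G(t)

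The understatement is G(t), the share of patients who have relapsed and are alive.

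Worked case, m = 12 and r = 6: λ = 0.05776, λ + μ = 0.06276, ν = 0.11552. S_C(24) = exp(−1.506) = 0.222. G(24) = 0.05776 × (0.0625 − 0.2217) / (0.06276 − 0.11552) = 0.174. S_D(24) = 0.396.

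| m (months) | OS as written (= PFS) | True OS, r = 3 | True OS, r = 6 | True OS, r = 12 |
|---|---|---|---|---|
| 12 | 22.2% | 29.6% | 39.6% | 54.8% |
| 18 | 35.2% | 42.3% | 50.7% | 62.7% |
| 24 | 44.4% | 50.8% | 57.8% | 67.7% |
| Understatement (points) | | 6.4 to 7.5 | 13.5 to 17.4 | 23.4 to 32.7 |

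A simulation of the r = 6 column (400,000 patients per scenario) gave 22.1 vs 39.6%, 35.1 vs 50.6% and 44.4 vs 57.9%, in agreement. Survival after relapse drives the gap more than time to relapse does.

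**Step 6. Scale against precision.** With 20 patients and no censoring, a survival proportion near 40% has a standard error of √(0.4 × 0.6 / 20) = 0.11, or 11 points. The error can be smaller or larger than that. Unlike sampling error, it always has the same sign.

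**The case against.** The strongest reply is that this is compressed drafting. The article condenses a fuller protocol that is not shown, it names PFS and OS as two measures, and the authors may simply have merged two definitions. That is plausible, and it means no one can say from this article that the final analysis will be wrong. It does not repair the sentence. The article states a definition that is wrong for one of the two endpoints it covers, which is different from leaving detail to another document. If the fuller protocol or the analysis plan defines OS correctly, the documents disagree and this one still needs correcting.

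Two stronger readings are tempting, and the text supports neither.

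- A reader might infer that relapses and transplants would be recorded as deaths. The sentence does not relabel them; it makes them events of the variable called OS.
- A reader might infer that survival after relapse could never be estimated. Nothing says that follow-up stops at relapse. Visits run to EOS and death until EOS is in the event list, so if vital status is collected to EOS, conventional OS could still be computed.

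It is also fair to say that the consequences are limited. PFS and OS are secondary and descriptive in a 20-patient single-arm phase I trial. The primary endpoints are adverse events and ELISpot response, and no stated test, threshold or decision uses OS. These points lower the severity but do not make the definition correct.

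**Conclusion.** The definition is wrong as written. Taken literally, OS is identical to PFS, and any patient alive after relapse counts as an OS event. The direction of the error follows from the definition alone: reported OS can only be too low.

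The size cannot be derived from the article. Under the stated exponential model it is roughly 6 to 33 percentage points at 24 months, depending mainly on how long patients live after relapse. These figures are an illustration, not an estimate for this population, and any transplants would add to the gap.

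Severity is moderate. The error makes one secondary endpoint unusable under its own name. It does not touch the primary endpoints, the sample size or the 10-of-20 rule, and it can be undone as long as deaths are recorded to EOS.

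**What to change.** Replace the shared clause with two definitions:

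- **PFS:** time from baseline (before first vaccination) to the earliest of leukemia progression, allogeneic transplantation or death from any cause, up to EOS. The present event set is kept for this endpoint only.
- **OS:** time from baseline to death from any cause. Patients not known to have died are censored at the date last known alive, at the latest EOS. Progression and transplantation are not OS events and do not end observation for OS.

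Check that the full protocol and the analysis plan use the same two definitions. The cost is one reworded sentence. The planned follow-up of about 26 months already supplies the window, and the only data requirement is vital status up to EOS, including after progression. Sample size and the decision rule need no change.

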## Discussion

5

Despite numerous treatment advances for AML in recent years and initially high remission rates, disease relapses occur in a large proportion of patients (1–3). The main reason for disease relapse is the presence of MRD mediated by therapy-resistant LPCs in the patient’s bone marrow (1, 3, 4, 7). Therefore, current efforts are focused on eliminating these cells to achieve long-lasting remissions and potential cures. A rational and promising approach to reach this goal is peptide-based immunotherapy, which represents a low side-effect treatment relying on specific immune recognition of HLA-presented peptides on the tumor cell surface (17, 18). Several peptide vaccination studies have reported promising results in terms of *in vivo* immunogenicity, but so far lack broad clinical responses (30–37). This is likely due to several so far unmet prerequisites for clinical effective peptide vaccination, including the selection of antigens, adjuvant formulations, combinatorial treatments and vaccination time points (18). We present here a first-in-human phase I, single-arm, open-label, interventional multi-peptide vaccination trial that aims to overcome these former limitations by addressing several key prerequisites for clinical effective vaccine design:

Based on our recent work characterizing the immunopeptidomic landscape of LPC in primary AML (23), we designed an AML/LPC peptide vaccine, comprising nine mutated and non-mutated AML- and AML/LPC-associated HLA class I- and HLA class II-restricted peptides. The non-mutated vaccine peptides were selected based on their high frequent natural presentation on AML blasts and particularly on LPCs in a large primary AML cohort. Furthermore, they were validated to be tumor-exclusive, as they were never detected on any benign tissue in an extensive benign immunopeptidome reference database (23). The mutated vaccine peptides comprise two HLA class I-restricted neoepitopes derived from a frameshift insertion in NPM1, which is the most common AML-specific mutation occurring in 35% of all AML patients (38), as well as an HLA class II-restricted neoepitope derived from the AML-specific mutation R140Q in IDH2. In stark contrast to previously conducted neoepitope-based peptide vaccination trials, in which the selection of vaccinated neoepitopes solely relies on *in silico* predictions (39, 40), the neoepitopes included in this vaccine were shown to be naturally presented on AML cells by mass spectrometry-based immunopeptidome analysis and to be targeted by memory T cell responses in AML patients. Of note, for both mutated and non-mutated AML antigens a correlation of HLA peptide presentation as well as peptide-specific memory T cell responses in AML patients with disease outcome was shown, which underscores the pathophysiological relevance of these antigens (23).

The AML-VAC-XS15 vaccine constitutes an off-the-shelf peptide vaccine mainly composed of HLA class II-restricted peptides with promiscuous binding to multiple HLA class II allotypes. The high promiscuity of HLA class II molecules enables the binding to and presentation of the vaccinated peptides by different HLA allotypes and therefore the HLA allotype-independent application of these peptides (41). The feasibility of this approach was recently proven in the P-pVAC-SARS-CoV-2 (NCT04546841) and B-pVAC-SARS-CoV-2 (NCT04954469) trials where 100% and 86% of participants developed a vaccine-induced peptide-specific T cell response independent of their HLA allotypes (25, 26). *In silico* binding predictions demonstrate that the HLA class II-restricted peptides included in the AML-VAC-XS15 vaccine should be able to bind to multiple HLA class II allotypes, which will enable universal patient coverage, in contrast to other approaches employing vaccines limited to particular HLA allotypes (42–44).

Beside the selection of optimal antigen targets, the use of a potent adjuvant formulation able to induce strong and long-lasting immune responses is a key prerequisite for efficient peptide vaccination. In the AML-VAC-XS15-01 study we apply an innovative immune stimulator adjuvant formulation based on the TLR1/2 agonist XS15 that has already proven safety and tolerability as well as potent T cell activation in clinical trials [NCT04546841 (25), NCT04954469 (26)]. XS15, a water-soluble derivative of the TLR1/2 ligand Pam3Cys (24), is combined with the peptide cocktail and emulsified with Montanide ISA 51 VG, resulting in an oily vaccine formulation for subcutaneous injection into the abdominal tissue. This formulation is designed to provide continuous immune stimulation without systemic side effects and has been shown to induce highly potent CD8^+^ and Th1 CD4^+^ T cell responses after single dosing, which exceed those elicited by other peptide and mRNA-based vaccines (25). In addition, the specific adjuvant formulation creates a depot at the injection site where the vaccinated peptides persist, thereby facilitating the induction of a robust immune response lasting up to several years (24–26, 45, 46). Importantly, so far no significant systemic side effects have been reported in healthy volunteers (NCT04546841) (25) or in cancer patients (46), in particular no allergic or anaphylactic reactions or immune-related side effects have occurred as yet.

Peptide vaccination will be applied in AML patients who have achieved CR with first-line therapy. This remission stage ensures an optimal effector-to-target cell ratio for peptide-based immunotherapy, as most of the tumor cells are eliminated and the T cell compartment should be recovered (47–49). Vaccination will start up to 20 weeks after completion of an intensive previous therapy. This time frame will give patients enough time to recuperate the immune system from first-line therapy. With patients receiving maintenance therapy due to an intermediate or high-risk situation, the shortest gap possible between reaching CR and the start of vaccination will be aimed for to minimize the risk of relapse while undergoing vaccination. Patients receiving continuous low-intensity therapy may enter the study as soon as CR/CRi has been achieved.

In summary, the AML-VAC-XS15 vaccine to be evaluated in this study promises to be an innovative treatment to prevent MRD-driven relapse in AML patients who have reached CR with standard therapy. For this particular patient population, which despite initial successes still faces a dismal prognosis, it is expected that the trial will demonstrate preliminary clinical efficacy of an effective, safe and easily applicable new therapeutic option.

